**Background**

Prevalence of diabetes mellitus, particularly type 2, is rapidly increasing worldwide and, though the rise is more pronounced in developing countries, Europe and North America are not spared by this “epidemics”. It has been estimated that there will be about 221 millions diabetic subjects in the world in 2010, as compared with the 124 millions patients estimated in 1997 [1]. As a consequence, also the burden of the invalidating long-term complications of diabetes is expected to rise, with an inevitable increase of the social and economic costs associated with the disease.

Diabetic subjects are in fact at higher risk for macro and microvascular disease than the general population [2]. The increased morbidity and mortality for cardiovascular disease (CVD) has been attributed to both chronic hyperglycemia *per se* and comorbid conditions occurring in diabetic patients more frequently than in nondiabetic subjects. These conditions include central obesity, dyslipidemia and arterial hypertension, which have been shown to cluster and associate with insulin resistance and disturbances of glucose metabolism, thus suggesting the existence of a unique pathophysiological condition, called “Metabolic Syndrome” (MS) or “insulin resistance syndrome” [3].

Sedentary habits have been associated with an increased prevalence of diabetes and MS. Moreover, a low cardiorespiratory fitness was shown to be a powerful and independent predictor of all-cause and CVD mortality in type 2 diabetic subjects [4-7]. Conversely, lifestyle-modification programs including physical activity were shown to prevent the development of type 2 diabetes in high risk subjects; this was associated with significant improvements in body weight, central adiposity, HbA1c and lipid levels, insulin sensitivity and prevalence of hypertension [8-13]. Moreover, in type 2 diabetic patients, a moderate or high level of physical activity (occupational, commuting, and leisure-time) reduced total and CVD mortality by improving glycemic control and other CVD risk factors [14,15].

The Italian Diabetes and Exercise Study (IDES) has been designed to evaluate the efficacy on modifiable CVD risk factors of a prescribed and supervised mixed (aerobic and resistance) training program, in addition to structured exercise counseling as part of conventional disease management, as compared with standard care alone (including structured exercise counseling), in type 2 diabetic subjects with the metabolic syndrome (MS).

# **Design and methods**

# **Study design**

# This study is a randomized controlled trial (ISRCTN-04252749). The protocol complies with the Declaration of Helsinki.

**Endpoints**

***Primary outcome***

The primary research goal is the evaluation of the efficacy of a mixed exercise training program, prescribed and supervised, as compared with standard care, in terms of reduction of HbA1c levels.

***Secondary outcomes***

Secondary research goals include an exploration of :

- Percentage of patients in each group that after 12 month achieve one or more of the following targets: HbA1c <6.5% or HbA1c reduction >0.5%; total cholesterol <175 mg/dl; LDL cholesterol <100 mg/dl; HDL cholesterol >40 mg/dl; triglycerides <150 mg/dl; systolic blood pressure (BP) <130 mmHg; diastolic BP <80 mmHg; BMI reduction >1; waist circumference reduction >5 cm.
- Difference between groups in terms of reduction of HbA1c, serum triglyceride and LDL-cholesterol, systolic and diastolic BP, BMI and waist circumference and increment of serum HDL-cholesterol.
- Difference between groups in terms of reduction of number and/or dosage of glucose-, lipid- and BP-lowering drugs.
- Difference between groups in terms of reduction of global cardiovascular 10-year risk (UKPDS risk engine tables).
- Difference between groups in terms of improvement of well-being.
- Difference between groups in terms of direct medical costs and direct and indirect social costs.
- Dose/response relationship between the quality (volume and intensity) of exercise training and modifiable cardiovascular risk factors.
- Relationship between physical fitness at baseline and during the study and modifiable cardiovascular risk factors.

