# On the third visit (R3), basal anthropometric and blood pressure (BP) measurements will be obtained and registered in the database, together with results of laboratory tests performed centrally. Subsequently all patients will receive a treatment regimen aimed at achieving optimal glycemic, lipid, BP and body weight targets, as established by current guidelines. This program will eventually include glucose-, lipid- and BP-lowering agents as needed and, when indicated, anti-platelet drugs. For ethical reasons, drugs will be also adjusted throughout the study to attain target levels and to account for reduced needs. The treatment regimen will include also a dietary prescription, which will be preceded by a preliminary nutritional evaluation with assessment of BMI and the individual patient requirements and preferences. The diet will contain 55% calories from complex carbohydrates, 30% from fat, and 15% from protein. Since all patients are overweight or obese, they will receive a low calorie diet (negative balance of 500 kcal/day, not <1500 Kcal in males and 1200 Kcal in females), calculated by adding the estimated energy expenditure from non-conditioning or non-volunteer and conditioning or volunteer physical activity to basal metabolism estimated using the gas exchange analyzer FitMate (Cosmed, Rome, Italy). Baseline LTPA will be calculated by multiplying the weekly hours spent in the various activities, as reported in the Minnesota LTPA questionnaire, by the metabolic equivalent (MET) score of each activity, and expressed as METs· h–1 · week–1. Patients will be also given a diary to be filled in daily with type of physical activity performed and time spent in each of them (Figure 2 and Table 4). Finally, patients will receive a list of intermediate, group B biochemical measurements, to be performed at each center laboratory immediately before the next visit (Table 3), will be prescribed.

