***Statistical analysis plan***

The c2 test for categorical variables and the Student’s t test or the corresponding nonparametric Mann-Whitney test for continuous variables will be utilized to compare patients’ characteristics at baseline. The efficacy of intervention on primary and secondary endpoints will be assessed using the unpaired t-test or the Mann Whitney U test for continuous variables, by comparing between-groups changes from baseline to end-of-study. For categorical variables (i.e. medications), logistic regression analysis will be applied, with end-of-study rate of use included in the model as the dependent variable and baseline rate of use and study arm included as covariates.

To account for change in medication throughout the 12-month period, multiple regression analysis will be performed, with baseline-to-end-of-study changes as dependent variable and treatment at baseline and treatment initiation during the study as dichotomous variables (yes versus no), whereas drug dosage will not be taken into consideration.

Within group end-of-study vs. baseline values will be compared using the McNemar test for categorical variables and the Wilcoxon signed ranks test for continuous variables. To identify independent predictors of HbA1c changes from baseline, a multiple regression analysis was applied, with mean value of METs, baseline HbA1c values, gender, age, and changes in HOMA-IR, BMI, waist, total, LDL-cholesterol and HDL-cholesterol, and hs-CRP as covariates forced in the model.

Multivariate analysis techniques (multiple or logistic regression) will be used to adjust for differences in the distribution of one or more parameters between the two arms, whereas the ANOVA trend test will be applied for evaluating the relationship of volume and intensity of exercise training (dose/response) and fitness variation with modifiable cardiovascular risk factors.

The likelihood to achieve glycaemic and nonglycaemic targets after 12 months will be estimated using logistic regression, adjusted for baseline status (on-target vs. not-on-target).

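### The drug-reduction outcome is defined on number and/or dosage, but the analysis named for medications models only end-of-study use, so dose reductions in patients who stay on a drug are not seen

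*Protocol*

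**What the plan says.** **Outcome.** The protocol's Secondary outcomes section includes the "Difference between groups in terms of reduction of number and/or dosage of glucose-, lipid- and BP-lowering drugs".

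**Analysis named for medications.** The Statistical analysis plan section puts medications among the categorical variables and assigns them a logistic regression. That model is specified "with end-of-study rate of use included in the model as the dependent variable and baseline rate of use and study arm included as covariates".

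**Other rules in that section.**
- Efficacy on primary and secondary endpoints is assessed "using the unpaired t-test or the Mann Whitney U test for continuous variables, by comparing between-groups changes from baseline to end-of-study".
- Within-group values are "compared using the McNemar test for categorical variables and the Wilcoxon signed ranks test for continuous variables".
- A multiple regression is meant to allow for medication changes. Its dependent variable is the change in the endpoint. Treatment at baseline and treatment initiation enter as yes/no terms, "whereas drug dosage will not be taken into consideration".

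**Conduct.** The account of visit R3 says that "drugs will be also adjusted throughout the study to attain target levels and to account for reduced needs". The Follow-up and final evaluation section has therapy changes entered in the study database, but does not say that dose is recorded.

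**The concern.** The outcome is a reduction in how many drugs a patient takes, in their dose, or in both. The variable modelled is whether the patient is using the drug at the end of the study. These are different quantities. The protocol is not silent here, so this is not detail left to a separate analysis plan: it names the dependent variable, the model and the covariates, and they do not match its own outcome.

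Both arms are treated toward targets and drugs are adjusted for reduced need. The protocol therefore anticipates reductions, and nothing in it suggests they will all be complete stops. Followed as written, the analysis could report no difference in medication while one arm had more dose reductions than the other.

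**Working it through.** **1. What the named variable can record.** Compare four patients between baseline and month 12:

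| Patient | Number of drugs | Dose | Use coded per class | Use coded per agent |
|---|---|---|---|---|
| A: no change | same | same | yes, yes | yes, yes |
| B: same agent, lower dose | same | lower | yes, yes | yes, yes |
| C: two agents in a class, one stopped | lower | same for the other | yes, yes | yes, no for the stopped agent |
| D: only agent in a class stopped | lower | stopped | yes, no | yes, no |

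B cannot be told from A under either coding. C cannot be told from A if use is coded per class, which is how the outcome groups the drugs. If use is coded per agent, C registers for the stopped agent. Even then, separate models per agent do not give the total: a switch from one agent to another appears as one stop and one start although the number is unchanged.

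**2. Whether another stated analysis covers number or dose.** The McNemar test is binary and within group. The medication-adjustment regression has the change in the endpoint as its dependent variable, with medication only as yes/no covariates. The t-test/Mann-Whitney rule does not name drug number or dose.

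**3. The plan's own figures.** The Sample size calculation section gives SD 1.6, difference 0.5, power 90% and α = 0.05:

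n per arm = 2 × (1.960 + 1.282)² × 1.6² / 0.5² ≈ 215.2, against 215 stated (216 if rounded up). It reproduces as a two-sided test.

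After 25% dropout, 600 × 0.75 = 450, or 225 per arm. This calculation concerns HbA1c. The section also claims more than 90% power for the changes indicated in the secondary endpoints, but no change is indicated for number or dosage of drugs, so that claim cannot be checked for this outcome.

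**4. Illustration of size (all rates assumed, none from the protocol).** Two-sided α = 0.05, with

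power = Φ{[δ√n − 1.96√(2p̄(1−p̄))] / √(p₁(1−p₁) + p₂(1−p₂))}.

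*Simple comparison of proportions, 225 per arm:*
- Any reduction, 20% vs 10%: (1.500 − 0.990)/0.500 = 1.02, power 85%.
- Half of these are complete stops, 10% vs 5%: (0.750 − 0.730)/0.371 = 0.05, power 52%.
- A quarter are complete stops, 5% vs 2.5%: (0.375 − 0.527)/0.268 = −0.57, power 29%.

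This does not model the stated regression, because it ignores baseline use and patients who start a drug.

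*Simulation of the stated logistic model, 225 per arm.* Assumptions: 80% on the class at baseline; any reduction in 30% (EXE) vs 15% (CON) of users; 15% of non-users start. Any reduction among baseline users, 0.8 × 225 = 180 per arm, has power (2.012 − 1.157)/0.581 = 1.47, about 93%. The stated model gives:

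| Share of reductions that are complete stops | Power, 400 simulated trials | Power, 2,000 simulated trials |
|---|---|---|
| 10% | 9% | 8% |
| 25% | 22% | 23% |
| 50% | 54% | 48% |
| 100% | 88% | 89% |

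The gap at 50% is compatible with simulation error: √(0.5 × 0.5/400) = 2.5 points for the shorter run. If no reduction is a complete stop, the modelled variable carries no signal.

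**The case against.** The strongest reply is that the section's general rule applies the t-test or Mann-Whitney test to changes in continuous secondary endpoints, and a drug count or a dose is numeric. That reading is possible, so it would be too much to say that the protocol rules out any analysis of number or dose. But the same paragraph puts medications among the categorical variables and gives them a model of their own, which points the other way.

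Four further limits stand:
- A reader might infer that dropping one of several drugs is always scored as no change. The document supports this only if use is coded per class, and it does not state the coding.
- A reader might take the clause that leaves dosage out as the protocol's rule for this outcome. It belongs to the regression that adjusts other endpoints for medication, so it is not evidence of how this outcome is analysed.
- A reader might quote one of the power figures as the loss in this trial. They rest on assumed rates, and the any-reduction figures are for a simple binary comparison, not for the analyses proposed under the fix.
- Medication expenses are part of direct medical costs (Assessment of costs), and the cost difference is itself a secondary outcome. That may reflect number and dose in part, but does not isolate them.

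**Conclusion.** The concern holds in a limited form. The analysis named for medications does not estimate the outcome as defined. The loss of dose reductions in patients who remain on a drug is certain if use is modelled as written. The loss of a reduction in the number of drugs within a class depends on the unstated coding. Under either coding, no stated analysis names the total number of drugs as its variable.

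The direction is clear: a yes/no variable cannot pick up partial reductions. The size depends on what share of reductions are complete stops, which the protocol does not give; over assumed shares of 10% to 100%, the simulated power of the stated model runs from about 8% to 89%. The finding itself does not depend on those rates.

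The severity is minor to moderate. The secondary goals are introduced as exploratory, this is one of several, and neither the HbA1c outcome nor its sample size is touched.

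**What to change.** In the Statistical analysis plan section, add for each drug class (glucose-, lipid- and BP-lowering):

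1. **Number.** Change from baseline to month 12 in the number of drugs is compared between arms with the plan's own rule for changes (Mann-Whitney), or by a regression adjusted for baseline number.
2. **Dose.** Where dose is recorded, change within the same agent is classed as decreased, unchanged or increased and compared between arms. A stated rule covers mixed changes, such as one agent stopped and another increased. Restricting the comparison to the same agent avoids needing a common dose scale across agents.
3. **Use.** The logistic model of end-of-study use is kept as a supporting analysis, and the text states whether use is coded per class or per agent.

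Alternatively, restate the item under Secondary outcomes as end-of-study use, so that outcome and analysis agree.

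The cost is a few sentences of text plus some derivation work from the registered therapy changes. The sponsor should first confirm that dose is captured; if it is not, the dosage part of the outcome cannot be analysed and should be dropped from its definition. No change to sample size or visits is needed.

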**Measurements**

***Assessment of physical fitness***

Parameters of physical fitness, i.e. cardio-respiratory fitness, strength and flexibility, will be evaluated at baseline and at the end of the study by the estimation of VO2max, a 5-8 maximal repetition (MR) and a standard bending, respectively. In the EXE Group, measurements will be performed also during the study period, in order to adjust the training loads according to improvements in fitness parameters.

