*Cardio-respiratory fitness.* Assessment of cardio-respiratory fitness will consist of a sub-maximal VO2max evaluation, i.e. at 80% of the predicted maximal heart rate (MHR = 220 – age). It has been preferred to a maximal test, because (a) the latter cannot be performed without a cardiologist, according to the Italian law; (b) heart rate varies linearly with VO2 to the point of maximum exertion, thus allowing extrapolation of the actual VO2max value. The test will be preceded by two consecutive run-in sessions to become familiar with testing devices and protocols, based on the results of a pilot study showing that tests executed during the first visit have a very low reliability, which increases significantly with tests executed at the third visit. All patients will perform the test at the treadmill, which has been preferred to the cyclo-ergometer to avoid early muscle exhaustion in untrained subjects, using a protocol modified form the Balke and Ware procedure [22] (Table 6), with direct oxygen consumption analysis and concurrent assessment of heart rate. According to our protocol, patients will walk two minutes at the speed of 4.3 Km/hour at 0 % gradient (warm-up), wearing the mask of a gas exchange analyzer FitMate. Then, protocol will proceed automatically through the steps indicated in Table 5 and terminate when the patient reaches the 80% of the predicted MHR and the metabolic fitness instructor stops the procedure using the dedicated key function on the gas analyzer. In the case of patients taking medications that affect heart rate, such as -adrenergic blockers, the Borg Rate of Perceived Exertion scale will be used (version 1-10). Patients will be stopped at the perceived value of 5-6 (hard) because, according to ACSM’s guidelines, this value corresponds to a heart rate of 70-89%. Test duration will range from 5 to 15 minutes. In the EXE group, this protocol will be repeated every three months with the same modalities and monthly without direct readings of oxygen consumption, in order to adjust the training load throughout the exercise period. For every step exceeding the previous evaluation, the predicted VO2max will be incremented of 2 ml of oxygen and the training load will be increased accordingly.

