*Strength.* For strength assessment, a RM test will be performed with the following modalities: thrust movement on the transverse plane (chest press or equivalent), traction movement on the frontal plane (lateral pull down or equivalent), and squat movement (leg press or equivalent). The 1RM test is the most reliable test for evaluating the maximal dynamic strength of a muscle or group of muscles. However, due the very low fitness profile of patients enrolled in this study, a MR test (or 5-8 RM test) has been preferred, for safety (to avoid maximal loads to the joint structures) and validity (untrained subjects are not always able to properly reach their 1RM) reasons. One RM will be then predicted from the weight loaded and the number of repetitions executed after a proper warm up using the Brzycki formula [23]. Results will be expressed as upper body (average of thrust movement and lateral pull down) and lower (leg press) body strength. In the EXE group, the MR test (with 5-8 repetitions) will be repeated every three months with the same testing machine to adjust the training load throughout the exercise period.

*Flexibility.* For hip and trunk flexibility assessment, a standard bending test will be executed. Standing on a step with legs fully extended, patients will be asked to bend the torso forward to try to touch the ground with their fingertips. The test will be performed three times and the distance between the finger and the ground will be measured by the exercise specialist at the third attempt.

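### Interim fitness is measured only in EXE, and the trend test of fitness change against risk factors has no arm term, so a pooled result can reflect arm alone

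*Protocol*

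**What the plan says.** - **Outcome.** Protocol, Secondary outcomes, introduces its list as exploratory. The last item is "Relationship between physical fitness at baseline and during the study and modifiable cardiovascular risk factors". It names no arm.
- **Tests in all patients.** Protocol, Assessment of physical fitness: fitness parameters "will be evaluated at baseline and at the end of the study by the estimation of VO2max" and by strength and flexibility tests. The follow-up section and Table 2 (visit F4) confirm the final assessment for all patients.
- **Tests in EXE only.** The same section continues: "In the EXE Group, measurements will be performed also during the study period, in order to adjust the training loads". For the treadmill: "In the EXE group, this protocol will be repeated every three months with the same modalities and monthly without direct readings of oxygen consumption". For strength: "In the EXE group, the MR test (with 5-8 repetitions) will be repeated every three months". No interim fitness test is specified for CON.
- **Analysis.** Protocol, Statistical analysis plan, assigns the ANOVA trend test to exercise volume and intensity and to "fitness variation with modifiable cardiovascular risk factors". The same sentence mentions multivariable adjustment, but for imbalances between the arms, and sets the trend test apart from it. No arm term, stratification by arm or restriction to one arm is stated.

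**The concern.** Two things do not fit together.

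First, the outcome reads as if fitness during the study were available for the whole trial population. Between baseline and month 12 it exists only in EXE, where it was collected to manage training.

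Second, the fitness measure that both arms do have, the change from baseline to month 12, is to be tested by a method that ignores arm. EXE patients should gain more fitness than CON patients, and their HbA1c and other risk factors should improve more. Arm therefore drives both variables. In a pooled test, any other effect of being in EXE (regular supervised contact, weight loss, drug changes) would appear as an effect of fitness. A reader could then take a restatement of the randomised comparison as separate evidence that fitness gain is what matters.

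**Working it through.** **Step 1. Who has which fitness test.** This assumes that monthly and three-monthly EXE treadmill tests share a visit when they coincide.

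| | CON | EXE |
|---|---|---|
| Treadmill, months 0 and 12 | 2 | 2 |
| Treadmill, months 1 to 11 | 0 | about 11 (gas analysis at 3, 6 and 9) |
| Strength, months 0 and 12 | 2 | 2 |
| Strength, interim | 0 | 3 |

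The change from baseline to month 12 exists in both arms. An interim analysis can be run only in EXE.

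**Step 2. Inputs for the pooled test.** The protocol gives no figure for the fitness outcome, so there is none to reproduce. Its sample-size section supplies the HbA1c inputs.
- HbA1c difference 0.5, SD 1.6. As background, the two-sided calculation at 90% power and 5% gives 216 per arm against the stated 215, so these inputs are read correctly.
- Arm effect on HbA1c: d = 0.5/1.6 = 0.3125 SD.
- Completers: 600 recruited, 25% dropout, so 600 × 0.75 = 450, or 225 per arm.
- Assumed, not in the documents: EXE raises fitness change by f = 0.5, 0.8 or 1.0 within-arm SD relative to CON, and fitness change and HbA1c change are unrelated within each arm.

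**Step 3. Correlation produced by arm alone.** With equal arms, the size of the pooled correlation is

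r = (f·d/4) / √[(1 + f²/4)(1 + d²/4)], where 1 + d²/4 = 1.0244.

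- f = 0.5: 0.0391 / √(1.0625 × 1.0244) = 0.037
- f = 0.8: 0.0625 / √(1.16 × 1.0244) = 0.057
- f = 1.0: 0.0781 / √(1.25 × 1.0244) = 0.069

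**Step 4. Chance of a result below 0.05.** By Fisher's transformation, z = atanh(r)·√(N − 3) and the rejection rate is Φ(z − 1.96) + Φ(−z − 1.96). With N = 450:

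| f (assumed) | z | Closed form | Simulation, pooled | Simulation, arm means removed |
|---|---|---|---|---|
| 0.5 | 0.79 | 12.4% | 12.3% | 5.3% |
| 0.8 | 1.21 | 22.8% | 23.6% | 4.7% |
| 1.0 | 1.46 | 31.0% | 30.7% | 5.3% |

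The simulation used 4000 replicates with 225 per arm.

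**Step 5. Range.** Taking f down to 0.2 gives r = 0.015. Over f = 0.2 to 1.0 the closed form gives 6% to 30% with 430 patients and 7% to 39% with 600. These are rates for one risk factor.

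A linear correlation test stands in here for the ANOVA trend test. A trend over fitness categories would behave similarly, with rates depending on the grouping.

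**The case against.** The strongest reply is that the protocol already contains most of the remedy. Both arms are tested at baseline and at the end, so fitness change can be computed for every completer, and that is the natural reading of the analysis section. The interim EXE tests have a stated training purpose, and nothing puts them into an outcome analysis. An arm term in an exploratory model is ordinary detail for an analysis plan that is not shown. The calculation also assumes the fitness gain, a zero link within arm, and a cross-sectional SD used as the SD of change.

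Much of this stands and limits the point. What remains is that the outcome wording still promises fitness during the study without restricting the arm, and that the protocol itself names the test for fitness change and separates it from the adjusted models. A pooled test run as written would mix the two effects.

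A reader might infer more than the documents support:

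- **That the whole outcome is confounded with arm.** Baseline fitness against risk factors is untouched by the interim schedule. An analysis of interim values lies within EXE and cannot be confounded by arm; its limit is the absence of CON data.
- **That frequent testing inflates fitness gains in EXE.** The pilot finding is that "tests executed during the first visit have a very low reliability, which increases significantly with tests executed at the third visit". That concerns reliability; no shift in the mean is reported. Two run-in sessions address it.
- **That an extra treadmill step adds 2 ml to the outcome.** That increment belongs to the EXE retests used to raise training load. Nothing says the baseline or final value is scored that way.
- **That run-ins are missing before the final test.** Table 2 lists the same single fitness appointment at R2 as at F4, so its silence shows nothing, and the run-in rule is not limited to baseline.
- **That Table 2 wrongly omits the EXE interim tests.** It lists clinic visits; those tests belong to the training programme.

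**Conclusion.** The point holds in a limited form. The outcome wording does not match the data collected, and the stated test of fitness change leaves out arm. A pooled analysis would then reject in about 12% to 31% of trials at a nominal 5%, with 225 per arm, an HbA1c effect of 0.31 SD, no link within arm and an assumed fitness gain of 0.5 to 1.0 SD. At a gain of 0.2 SD the excess is about one percentage point. If the SD of HbA1c change is below 1.6 the excess is larger, and if above, smaller. The spurious correlation itself stays small, at most 0.07 in this range.

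This is a modest bias in an exploratory secondary goal. It leaves the primary HbA1c comparison untouched and is worth correcting because the correction is cheap.

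**What to change.** 1. In Secondary outcomes, define the item on two quantities that both arms have: baseline fitness, and the change in fitness from baseline to month 12.
2. In Statistical analysis plan, state that the relationship of fitness change to each risk factor is estimated within arm, or in a model that includes arm.
3. State that interim fitness values are reported descriptively as EXE-only data, outside this outcome.

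The cost is a few sentences and one model term, with no new data. The statistical price is that the between-arm contrast in fitness no longer informs the slope. With equal arms the fitness variance falls from 1 + f²/4 to 1, so, leaving aside any gain from a smaller residual variance, the standard error rises by a factor √(1 + f²/4): 1.03 at f = 0.5, 1.08 at 0.8 and 1.12 at 1.0. That is a small loss, and what it gives up is the contrast that cannot separate fitness from the other effects of being in EXE. The association within arm remains observational and should be described as such.
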